**SYNOPSIS**

**Title：Allo-DNT Cells for the Prevention of Relapse in AML Patients After Allo-HSCT**

**Objective**

To evaluate the safety and tolerability of healthy donor-derived double negative T cells (DNTs) infusion in acute myeloid leukemia (AML) patients after allogeneic hematopoietic stem cell transplantation (allo-HSCT).

**Trial Design**

This is a phase 1/11 study to assess the safety and efficacy of healthy donor-derived DNTs in AML patients after allo-HSCT. The trial is divided into two parts: Part A is a dose escalation trial with two dose groups (1.0×10^8 cells/kg, 1.5×10^8 cells/kg at day 0, day 28 and day 56), with 6-12 patients planned to be enrolled. Part B is a dose-expansion randomized controlled trial in which 40-60 patients will receive RC1012 infusions at recommended phase II dose (RP2D) levels.

**Patient Population**

AML patients after allo-HSCT are eligible for enrollment.

**Sample Size**

We plan to recruit 6-12 patients.

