Allo-HSCT can induce a curative graft-versus-leukemia (GVL) effect, but it may also lead to other diseases or mortality due to donor T cells attacking the recipient’s normal cells and tissues. Previous studies have confirmed that the infusion of allogeneic mouse DNT cells into NSG mice does not cause GvHD and can suppress GvHD caused by the transplantation of CD4^+^ and CD8^+^ T cells from the same allogeneic source(7). Similar to mouse DNT cells, human DNT cells can also inhibit the in vitro proliferation of corresponding CD4^+^ and CD8^+^ T cells. In patients who received allo-HSCT, a higher frequency of DNT cells has been associated with reduced severity of GvHD, suggesting the potential therapeutic benefits of DNT cell treatment(8). To verify the effects of in vitro-expanded human DNT cells in a GvHD setting, DNT cells and/or PBMCs from different donors were intravenously infused into NSG mice, and the incidence of GvHD was observed. Consistent with previous reports, mice infused with human PBMCs developed severe acute GvHD, manifested by weight loss. Histological analysis of the PBMC-infused mice revealed acute GvHD lesions in multiple organs. However, in mice infused with an equivalent or fourfold higher number of DNT cells compared to PBMCs, although lymphocytic infiltration was observed, there was no weight loss, and no organ damage was found in the liver, lungs, or intestines. Even 50 days after DNT cell infusion, the mice still showed no signs of GvHD. In summary, these studies suggest the safety of RC1012 injections (with DNT cells as the main component).

Collectively, our data indicate that DNT cells is a novel off-the-shelf adoptive cellular therapy (ACT) against AML. Based on these preclinical data, this trial intends to enroll 6~12 patients to assess the safety and efficacy of increasing the dose of DNT cells in the prevention of AML patients after allo-HSCT.

1. **OBJECTIVES**

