**2.2 Secondary Objectives**

- Pharmacokinetics (PK) indicator (Cmax)

The peak concentration of allo-DNT cells amplified in the peripheral blood (Cmax, detected by Flow Cytometry). Time Frame: Up to 2 years.

- Pharmacokinetics (PK) indicator (AUC)

Allo-DNT cells blood concentrations will be measured at different time points to evaluate the area under the curve (AUC). (AUC, detected by Flow Cytometry). Time Frame: Up to 2 years.

- Pharmacokinetics (PK) indicator (Tmax)

Allo-DNT cells blood concentrations will be measured at different time points to evaluate the peak time (Tmax) in peripheral blood. Tmax is defined as the time to reach the highest concentration (Tmax, detected by Flow Cytometry). Time Frame: Up to 2 years.

- Pharmacokinetics (PK) indicator (T1/2)

Allo-DNT cells blood concentrations will be measured at different time points to evaluate the elimination half-life in hours (T1/2). T1/2 is defined as the time point when the concentration of allo-DNT reaches half of maximum in a patient’s peripheral blood (T1/2, detected by Flow Cytometry). Time Frame: Up to 2 years.

- Recurrence rate at 6 months

Record the proportion of patients with recurrence in the study. Time Frame: Up to 6 months.

- Relapse-free survival (RFS)

Relapse-free survival is the time from study enrollment until documented disease relapse, or death from any cause. Time Frame: Up to 2 years.

- GvHD-free and relapse-free survival (GRFS)

GRFS is the time from study enrollment until documented disease relapse, or death, or GvHD occur from any cause. Time Frame: Up to 2 years.

- 2-year overall survival

From the date of entry into the clinical study until death from any cause. Time Frame: Up to 2 years.

1. **TRIAL DESIGN**

The trial is divided into two parts: Part A is a dose escalation trial with two dose groups (1.0×10^8 cells/kg, 1.5×10^8 cells/kg at day 0, day 28 and day 56), with 6-12 patients planned to be enrolled. Part B is a dose-expansion randomized controlled trial in which 40-60 patients will receive RC1012 infusions at recommended phase II dose (RP2D) levels. Patients at the end of the infusion will continue to be followed up for a total of 2 year.

1. **ELIGIBILITY**
   1. **Subject Eligibility**
      1. **Inclusion Criteria**

- Voluntarily sign an ICF and expect to complete the study procedures for follow-up examinations and treatment.
- Aged 18 to 70 years (including cut-offs), regardless of gender.

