- Investigators qualification: Investigators participating in clinical trials must be checked qualification and have the professional background and ability to conduct clinical trials.
- Training of researchers: Receiving training programs arranged by clinical trial institution for each project is a prerequisite to qualify investigators. After the approval of the medical ethics committee, the Principle Investigator (PI) will organize training.
  1. **Clinical Monitors**

Representatives of the Sponsor will conduct a site initiation visit and periodically audit, at mutually convenient times during and after the study, all CRFs and corresponding source documents for each subject. The monitors will verify that investigational products are properly stored and accounted for, verify that subjects’ consent for study participation has been properly obtained and documented, confirm that research subjects entered into the study meet inclusion and exclusion criteria.

- 1. **Standardized Operation**

The sponsor complies with the Drug Clinical Trial Quality Management Standard (2003 edition) and the Drug Registration Regulations. DNTs will be expanded ex vivo under GMP condition. Ensure the high quality for them.

- 1. **Laboratory Examination**

The research center will conduct laboratory tests in accordance with standard operating procedures (SOP).

1. **DATA HANDLING AND RECORD KEEPING**
   1. **Data Collection**

The Case Report Form (CRF) will comprise a set of forms capturing details of eligibility, baseline characteristics, treatment and outcome details etc. All entries will be entered into an electronic data capture system (EDC). PI is responsible for assuring that the data entered into eCRF is complete, accurate, and that entry and updates are performed in a timely manner.

- 1. **Data Retention**
- It is the investigator’s responsibility to retain study original documents. Original data include original records, informed consent signed by subjects, laboratory data, imaging data, ECG, medication records, etc.
- The researchers center should keep the basic data of subjects for a longer time according to the regulations (at least 5 years).

1. **SAMPLE SIZE**

Part A is a dose escalation trial with two dose groups, 6-12 patients planned to be enrolled. Part B is a dose-expansion randomized controlled trial in which 40-60 patients will receive RC1012 infusions at RP2D dose levels.

1. **REFERENCE**

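### The Sample Size item in the synopsis and the Background give 6-12 patients for the trial, but the design sections use that number for Part A only and add a randomized Part B of 40-60

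*Protocol*

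**What the plan says.** Two places give one range for the trial as a whole:

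- Synopsis, Sample Size: "We plan to recruit 6-12 patients". This is the entire item.
- Section 1, Background, last paragraph: "this trial intends to enroll 6~12 patients to assess the safety and efficacy of increasing the dose of DNT cells".

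Three places give that range to Part A and add a second part:

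- Synopsis, Trial Design: "with 6-12 patients planned to be enrolled. Part B is a dose-expansion randomized controlled trial in which 40-60 patients will receive RC1012 infusions".
- Section 3, Trial Design: the same 6-12 for Part A, then "Part B is a dose-expansion randomized controlled trial in which 40-60 patients will receive RC1012 infusions".
- Section 10, Sample Size: "Part A is a dose escalation trial with two dose groups, 6-12 patients planned to be enrolled", followed by "Part B is a dose-expansion randomized controlled trial in which 40-60 patients will receive RC1012 infusions at RP2D dose levels".

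No section gives a combined total, the number of Part B controls or the allocation ratio.

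**The concern.** Planned enrolment is a core protocol parameter, and here it has two values. On the Sample Size item and the Background sentence, this is a small uncontrolled dose-escalation study. On Section 10, at least 40 further patients receive an allogeneic cell product within a randomized comparison. A reader who relies on the item headed Sample Size learns nothing of the larger part.

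The difference also affects what the trial can show. Section 6.1 names the 6-month cumulative relapse rate as the main outcome, and the Background sentence attaches both safety and efficacy to 6-12 patients. A group of that size gives a very wide interval for a relapse proportion and contains no randomized comparison.

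The absence of a power or precision calculation is not part of this point, because it may be in the statistical analysis plan. The point is only that statements within the protocol disagree.

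**Working it through.** **Inputs.** Part A 6-12 and Part B 40-60 (synopsis Trial Design, Section 3, Section 10). Trial total 6-12 (synopsis Sample Size, Background). No sample-size formula is given, so the only check on the stated figure is whether the parts add up to it.

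**Step 1: add the parts.**

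- Lower end: 6 + 40 = 46, against a stated 6.
- Upper end: 12 + 60 = 72, against a stated 12.
- Excess over the stated maximum of 12: 46 − 12 = 34, and 72 − 12 = 60.

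The stated 6-12 is not reproduced as a trial total. It is reproduced as Part A alone: Section 2.1 defines the MTD by DLTs in at most 1 of 6 subjects, and two dose groups of up to 6 make 12. The lower figure of 6 fits two groups of 3, where 3 per dose is an assumption.

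**Step 2: allow for controls.** Part B is called a randomized controlled trial, yet the 40-60 are described as patients who receive RC1012. Taken literally, the controls are extra. The total is then Part A + Part B × (1 + controls per RC1012 patient):

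| Reading of 40-60 | Lower total | Upper total |
|---|---|---|
| Both arms together | 6 + 40 = 46 | 12 + 60 = 72 |
| RC1012 only, assumed 2:1 | 6 + 40 × 1.5 = 66 | 12 + 60 × 1.5 = 102 |
| RC1012 only, assumed 1:1 | 6 + 40 × 2 = 86 | 12 + 60 × 2 = 132 |

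**Step 3: illustrate the effect on precision.** Assume a relapse proportion of about 30%, taken from the Background figure of more than 30% after transplant. Exact (Clopper-Pearson) 95% intervals are:

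| Relapses / patients | 95% interval | Half-width (points) |
|---|---|---|
| 2/6 | 4% to 78% | 37 |
| 4/12 | 10% to 65% | 28 |
| 12/40 | 17% to 47% | 15 |
| 18/60 | 19% to 43% | 12 |
| 14/46 | 18% to 46% | 14 |
| 22/72 | 20% to 43% | 11 |

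Unrounded, the half-width ratio is 36.7/14.0 = 2.6 for 6 against 46 patients, and 27.6/11.1 = 2.5 for 12 against 72.

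These intervals are illustrative only. The Background figure has no 6-month horizon and describes AML patients generally, while this trial enrols high-risk patients without relapse at 60-100 days after transplant. The counts 2/6 and 4/12 are 33%, the nearest to 30% that those sizes allow. The rows for 46 and 72 pool Part A with Part B, and so pool dose levels and possibly arms.

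**The case against.** The best defence is that Section 10, the body section on sample size, splits the numbers clearly and agrees with Section 3. The synopsis Trial Design says the same two items above the Sample Size line, so a reader of the synopsis has already met the two-part design. The Background sentence speaks of increasing the dose, which fits Part A. On this view 6-12 is a leftover Part A number that any careful reader will understand.

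Much of this stands. It is the likely origin of the discrepancy, and the conflict is not one of synopsis against body, since the synopsis carries both versions. But neither the Sample Size item nor the Background sentence says Part A, the Background makes the trial its subject, and no other text reconciles the two.

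A reader might also infer more than the documents support:

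- *That what can be concluded on relapse differs six-fold.* Six-fold is the ratio of the upper totals only (72/12); the lower totals differ 46/6 = 7.7-fold. Interval width differs about 2.5-fold, and the more important loss is the randomized comparison.
- *That the design assigns efficacy to Part B.* No section does. The synopsis Trial Design gives safety and efficacy for the whole study, Section 2.2 lists the relapse and survival outcomes without naming a part, and only DLT and MTD are restricted to phase I (Section 6.3).
- *That the Sample Size line fixes the analysis denominator.* Analysis populations do that, and they commonly belong to the statistical analysis plan.
- *That 12 is a cap which prevents Part B from opening.* The line states a plan to recruit, not a limit.

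**Conclusion.** The contradiction stands. Two statements give 6-12 for the trial, and three give 6-12 for Part A plus a randomized Part B. The stated sample size therefore omits Part B and falls short of the sum of the parts by 34-60 patients, measured from its maximum of 12.

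The 46-72 is a sum made here, not a protocol figure. It is the whole-trial total only if the 40-60 include the controls. If they do not, the total is 66-102 or 86-132 under the allocation ratios assumed above, and the gap is larger. The precision figures rest on an assumed 30% and show scale only.

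This is an internal inconsistency in a key design parameter. It is not evidence that either design is wrong. It should be corrected, because the item that readers consult for trial size gives only the Part A number.

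**What to change.** 1. Replace the synopsis Sample Size line with three figures: Part A 6-12; Part B by arm, stating whether 40-60 counts RC1012 recipients only or both arms; and one overall total that includes controls.
2. In the last paragraph of Section 1, limit the 6-12 to Part A. Do not move efficacy to Part B in the same edit, since that would be a new design decision and not a reconciliation.
3. Use the same figures in the synopsis Trial Design, the synopsis Sample Size, Section 1, Section 3 and Section 10.
4. If only 6-12 patients are in fact intended, remove Part B throughout and report relapse and survival descriptively.

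The cost is a few sentences in a protocol amendment. Items 1 to 3 add no patients or procedures beyond those Section 10 already plans. The one fact the sponsor has to supply is the size of the Part B control arm.

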**Main Inclusion and Exclusion Criteria**

**Patient inclusion criteria**

- Voluntarily sign an ICF and expect to complete the study procedures for follow-up examinations and treatment.
- Aged 18 to 70 years (including cut-offs), regardless of gender.
- Subject must be diagnosed with AML according to World Health Organization (WHO) criteria (2016).
- The subject has received an allo-HSCT within 60-100 days, the percentage of malignant primitive cells in the bone marrow is < 5% after HSCT and STR-PCR shows complete donor chimerism.
- The subject has one of the following high-risk factors for relapse after allo-HSCT: (1) Failure to achieve remission after two courses of induction chemotherapy. (2) Prior history of Myelodysplastic Syndromes (MDS) or Myeloproliferative Neoplasm (MPN). (3) High leukocytes (≥100×10^9/L) combined with Central Nervous System Leukemia (CNSL); (4) Positive Minimal Residual Disease (MRD) before HSCT; (5) Non-remission or disease progression prior to HSCT; (6) Subject with cytogenetic high-risk factors (except that who can be treated with targeted drugs).
- The subject has recovered from the toxicity of the prior treatment, i.e., CTCAE toxicity grade <2 (unless the abnormality is tumor-related).
- ECOG score 0 to 1.
- With appropriate organ function.

**Patient exclusion Criteria**

- Subject is confirmed to have morphological relapse of leukemia or positive MRD after allo-HSCT.
- Subject with extramedullary infiltration of leukemia.
- Suffer from other malignancies within 5 years prior to screening, except adequately treated carcinoma in situ of the cervix, basal cell or squamous epithelial cell skin cancer, post-radical thyroid cancer, and post-radical ductal carcinoma in situ.
- Has severe respiratory disease.
- A previous history of a definite neurological or psychiatric disorder, including epilepsy or dementia.
- Evidence of active central nervous system invasion or cranial neuropathy.
- Patients with positive hepatitis B surface antigen (HBsAg) or hepatitis B core antibody (HBcAb) and peripheral blood hepatitis B virus (HBV) DNA titration assay not within the normal reference range, positive hepatitis C virus (HCV) antibody and peripheral blood HCV RNA ,positive for human immunodeficiency virus (HIV), or positive for cytomegalovirus (CMV) DNA, or positive syphilis test.
- Subject who is allergic to the excipients of RC1012 injection or other drugs recommended in the study protocol (e.g., tolimumab, etc.).
- Serious cardiac disease, including but not limited to severe arrhythmia, unstable angina, massive heart attack, New York Heart Association class III or IV cardiac insufficiency, refractory hypertension.
- Persons who have previously received an organ transplant or are preparing to receive an organ transplant (except for HSCT).
- Subject who has received other maintenance therapy drugs after HSCT or who wish to receive other maintenance therapy.
- Subject with the presence of acute GvHD of degree III to IV or extensive chronic GvHD.
- Active neurological autoimmune or inflammatory diseases (e.g. Guillain-Barre Syndrome (GBS), Amyotrophic lateral sclerosis (ALS)).
- Clinically significant active cerebrovascular disease (e.g. cerebral oedema, Posterior Reversible Encephalopathy Syndrome (PRES)).
- Subject with a life expectancy of less than 3 months.
- Subject has been involved in other clinical studies within 3 months prior to screening.
- Subject in the judgement of the investigator and/or clinical criteria, is contraindicated to any study procedure or have other medical conditions that may place them at unacceptable risk.

**Donor inclusion criteria**

- Age ≥ 18 years old.
- Healthy person who meet the requirements of blood donation in central blood station.
- There is no disease that can be transmitted through blood within 30 days before blood collection (HIV, HBsAg, HBcAb, HCV antibody, syphilis serological test, CMV IgM, and EBV IgM all negative).
- The cytotoxicity of DNTs to at least three myeloid leukemia cell lines (OCI-AML3, MV 4-11, K562, U937, etc.) (target to efficiency ratio 4:1) ≥ 20%, or to patient primary AML cells ≥ 10%.

**Donor exclusion criteria**

- There are chronic diseases that need to be treated, such as hypertension, diabetes, heart disease, thyroid disease and liver and kidney insufficiency.
- Bone marrow diseases.
- Pregnancy.
- Systemic glucocorticoids must be used before peripheral blood taking.
- Paroxysmal psychosis.
- Poison and drug addiction.

**Trial Schema**

[figure not shown]

9.1 Data Collection16

9.2 Data Retention16

**10 SAMPLE SIZE** 16

**11 REFERENCE**17

**12 APPENDIX**18

1. **BACKGROUND**

Acute myeloid leukemia (AML) is a heterogeneous hematologic malignancy characterized by abnormal proliferation, differentiation, and clonal expansion of hematopoietic stem/progenitor cells that invade the bone marrow, blood, and extramedullary tissues. Allogeneic hematopoietic stem cell transplantation (allo-HSCT) is currently the primary curative approach for relapsed/refractory AML, but more than 30% of AML patients experience post-transplant relapse. Relapsed patients have a poor prognosis, with a two-year overall survival rate of less than 15%, and relapse is a major cause of post-transplant mortality(1). High-risk factors for relapse include complex karyotype, TP53 gene mutations, failure to achieve complete remission after two cycles of induction chemotherapy, and minimal residual disease (MRD) positivity before transplantation. Despite allo-HSCT being the primary curative approach for relapsed/refractory AML, more than 30% of patients relapse after transplant. The prognosis for relapsed patients remains poor, with a two-year overall survival rate of less than 15%, making relapse the leading cause of post-transplant mortality(2). So far, the main strategies for preventing post-transplant relapse include optimizing conditioning regimens, improving GvHD prevention protocols, post-transplant maintenance therapy, and prophylactic donor lymphocyte infusion (DLI)(3).

DNT cells are a subset of mature T lymphocytes, constituting about 1-5% of peripheral blood mononuclear cells (PBMC) in mice, rats, and humans. DNT cells express CD3 and γδ-TCR but do not express CD4, CD8, or NK cell markers, nor do they bind to the invariant natural killer T cell (iNKT)-specific αGalCer-loaded CD1d tetramer(4). Therefore, they are distinct from conventional T cells, NK cells, and NKT cells. [name]’s laboratory at the University of Toronto was the first in the world to report the characteristics of antigen-specific DNT cells with transplant immune tolerance, and they conducted extensive studies on how these cells differ from traditional CD4^+^ or CD8^+^ T cells. Notably, transplantation of allogeneic DNT cells into mice not only did not induce graft-versus-host disease (GvHD) but also suppressed GvHD caused by allogeneic CD4^+^ and CD8^+^ T cells(5).

To determine the anti-leukemic function of DNT cells, RuiChuang Biotech evaluated the cytotoxicity of DNT cells expanded in vitro from healthy donors (HD) against blast cells derived from the peripheral blood of AML patients. The study found that after co-culturing these cancer cells with DNT cells expanded from HDs, DNT cells were able to kill AML cells in over 70% of the patients, exhibiting a dose-dependent killing effect. Additionally, the anti-leukemic activity mediated by DNT cells was higher than that of NK cells and CD8^+^ T cells. Using a patient-derived xenograft (PDX) model for AML, [name]’s lab discovered that, compared to the PBS-treated control group, a single infusion of allogeneic DNT cells from healthy donors significantly reduced the levels of CD45^+^CD33^+^ leukemic cells, previously engrafted into the bone marrow of mice from AML patients(6). Similar results were observed in experiments involving three additional infusions of AML blasts and three different HD-derived DNT cells expanded in vitro. A single infusion of RC1012 solution reduced the AML blast burden in the experimental mice, and two additional infusions of DNT cells administered every three days further decreased the leukemic burden, demonstrating that multiple infusions of DNT cells enhanced the therapeutic efficacy.

Allo-HSCT can induce a curative graft-versus-leukemia (GVL) effect, but it may also lead to other diseases or mortality due to donor T cells attacking the recipient’s normal cells and tissues. Previous studies have confirmed that the infusion of allogeneic mouse DNT cells into NSG mice does not cause GvHD and can suppress GvHD caused by the transplantation of CD4^+^ and CD8^+^ T cells from the same allogeneic source(7). Similar to mouse DNT cells, human DNT cells can also inhibit the in vitro proliferation of corresponding CD4^+^ and CD8^+^ T cells. In patients who received allo-HSCT, a higher frequency of DNT cells has been associated with reduced severity of GvHD, suggesting the potential therapeutic benefits of DNT cell treatment(8). To verify the effects of in vitro-expanded human DNT cells in a GvHD setting, DNT cells and/or PBMCs from different donors were intravenously infused into NSG mice, and the incidence of GvHD was observed. Consistent with previous reports, mice infused with human PBMCs developed severe acute GvHD, manifested by weight loss. Histological analysis of the PBMC-infused mice revealed acute GvHD lesions in multiple organs. However, in mice infused with an equivalent or fourfold higher number of DNT cells compared to PBMCs, although lymphocytic infiltration was observed, there was no weight loss, and no organ damage was found in the liver, lungs, or intestines. Even 50 days after DNT cell infusion, the mice still showed no signs of GvHD. In summary, these studies suggest the safety of RC1012 injections (with DNT cells as the main component).

Collectively, our data indicate that DNT cells is a novel off-the-shelf adoptive cellular therapy (ACT) against AML. Based on these preclinical data, this trial intends to enroll 6~12 patients to assess the safety and efficacy of increasing the dose of DNT cells in the prevention of AML patients after allo-HSCT.

1. **OBJECTIVES**

